### 6.8.4 Serum Lactate Test (Cohort A Only)

A serum lactate level that measures the amount of lactic acid in the body will be obtained at Day 1 and EOT/ET (Visit 4).

Also in association with moderate exercise, capillary blood lactate level is to be measured by earlobe puncture just before starting, immediately after and 5, 10, 20, and 30 minutes after the 6MWT. Detailed instructions will be provided in the Laboratory Manual.

## 6.9 Pharmacokinetic Assessments

Not applicable.

## 6.10 Exploratory Assessments (Cohort A Only)

Blood samples for exploratory biomarker assessment will be obtained according to schedule at Day 1 and EOT/ET (Visit 4) and sent to the central laboratory for analysis. The analytes are indicated in

APPENDIX 3.

For ALL subjects in the study, predose blood samples will be collected at Day 1 and at EOT/ET (Visit 4). Blood samples for AA concentration are to be collected no more than 30 minutes before administration of study drug and after a fast (minimum duration) of 10 hours although water is permitted. The actual date and time (24-hour clock time) of each sample will be recorded in the eCRF. Plasma concentration of AAs will be analyzed by validated liquid chromatography with tandem mass spectrometry method. Details of the blood collection, processing, and handling samples and the analytical methods will be provided in the Laboratory Manual.

# 7 STATISTICAL CONSIDERATIONS

## 7.1 Sample Size Estimation (Cohort A and B)

**Cohort A**

The sample size calculation is based on the primary efficacy endpoint, the mean change from baseline at Week 4 in the PCr recovery rate. Based on literature review, the standard deviation (SD) of both the AXA1125 and the placebo group is assumed to be 10 seconds. To detect a clinically meaningful difference of 10-second improvement, approximately 32 subjects will provide 80% power at a 2-sided, 5% significance level. Assuming 20% dropout rate, approximately 40 subjects (20 subjects per arm) will be enrolled in this study.

This sample size will also allow for a general assessment of safety and tolerability of AXA1125 in this population. **Cohort B** Approximately 10 subjects (5 subjects per arm), who were considered screen-failures for Cohort A due to their PCr recovery rate constant (< 50seconds) provided their CFQ-11 is ≥ 8 and they meet all the eligibility criteria will be enrolled in this Cohort.

## 7.2 Populations for Analysis (Cohort A and B)

### 7.2.1 Intent-to-treat analysis set

The intent-to-treat (ITT) population will consist of all subjects randomized who received at least 1 dose of the study drug. Subjects will be assessed according to their randomized treatment regardless of the treatment they received. The primary population for efficacy analyses is the ITT analysis set.

### 7.2.2 Safety analysis set

The Safety Analysis Set will include all subjects who receive at least 1 dose of study drug. Subjects in the Safety Analysis Set will be analyzed by the treatment received on Day 1. The primary population for safety analyses is the Safety Analysis Set.

### 7.2.3 Per-protocol analysis set

The per-protocol (PP) analysis set will include all subjects in the ITT population without any major protocol deviations. All analyses performed in the PP analyses set will be considered as sensitivity analyses.

### 7.2.4 Pharmacokinetic analysis set (Cohort A)

The PK Analysis Set will comprise all subjects in the Safety Analysis Set who have evaluable PK concentration data for at least 1 AA.

## 7.3 Study Endpoints (Cohort A and B)

The study endpoints are presented in Section 2.3.

## 7.4 Statistical Methods (Cohort A and B)

### 7.4.1 General approach

Descriptive statistics for continuous variables will include the number of subjects with data to be summarized, mean, SD, median, and range (minimum, maximum).

All categorical/qualitative data will be presented using frequency counts and percentages.

The statistical methods for comparison of each endpoint and complete missing imputation methods will be detailed in the Statistical Analysis Plan (SAP), which will be developed and completed prior to database lock.

There will be no multiplicity adjustment and all analyses will be performed at the 2-sided 0.05 level of significance.

### 7.4.2 Randomization and blinding

At Visit 2, eligible subjects will be randomized through an IRT system into 1 of 2 groups (33.9 g BID AXA1125 or placebo BID) at a treatment allocation ratio of 1:1.

This is a double-blind study design. The subject, investigators, study site personnel involved in direct care of the subject will be blinded to treatment assignment. Personnel involved in the laboratory and image analysis will also remain blinded to the treatment assignment. The Sponsor study team members will remain blinded to the treatment assignments during the study. A Sponsor biostatistician will be unblinded to perform the interim analysis and data monitoring. See Section 5.1.6 for details on blinding.

#### 7.4.2.1 Breaking the blind

The PI is responsible for the medical care of subjects during the study. In an emergency, when knowledge of the subject’s treatment assignment is essential for the clinical management or welfare of the subject, the PI can unblind the treatment information for the subject through the IRT system. The unblinding should only occur for the subject in question if it is critical for treatment decision making by the PI for the well-being of the subject.

Prior to unblinding the subject’s treatment assignment, the PI should assess the relationship of an AE to the study drug (yes or no). In the vast majority of cases, AEs may be properly managed without the need for unblinding. If unblinding is warranted, the PI must then follow the appropriate procedures to unblind an individual subject’s treatment assignment. Generally, blinding should only be broken for events that are considered to be serious, unexpected, and causally related to the study drug, or as requested by the regulatory authority.

If the study blind is broken, the PI must detail the date and reason for unblinding in the subject’s records. The PI must also notify the Sponsor and if applicable, the regulatory authority, that the study blind has been broken. If the blind is broken due to an AE, the AE form must be completed and reported to the Sponsor.

### 7.4.3 Handling of dropouts/missing data

For binary endpoints, both worst-case and observed-case methods will be applied as the missing imputation method. Worst-case method is defined as subjects with missing data due to any reason will be considered as not meeting the endpoint. Observed-case imputation method is defined as subjects with missing data will not be included in the analysis. For continuous endpoints, both single and multiple missing imputations will be applied.

To address each of potential intercurrent events, the strategies will be detailed in the SAP, if appropriate.

### 7.4.4 Subject disposition

The number of subjects in each study population will be provided. The number and percentage of subjects who prematurely discontinue study drug along with disposition (completed study or early withdrawal, with breakdown for reasons for withdrawal) will be summarized. The denominator will be the number of subjects in the ITT population.

### 7.4.5 Demographics and baseline characteristics

Subject demographics and baseline characteristics, including age, sex, race, ethnicity, weight, height, and BMI will be summarized using descriptive statistics. Continuous data will be summarized with mean, SD, median, minimum, and maximum values. Categorical data will be summarized with frequency counts and percentages.

“Baseline” is defined as the most recent assessment prior to randomization.

Medical history and concomitant medications will be summarized.

### 7.4.6 Safety analyses

The safety data will be presented as individual listings and summary tables, including frequency tables for AEs and frequency and shift tables for laboratory evaluations, vital signs, and physical examinations. Shift tables will be generated for key safety parameters and graphical presentations will be utilized as needed.

AEs will be coded using the Medical Dictionary for Regulatory Activities (MedDRA). Summary tables for AEs will include all TEAEs, related TEAEs, SAEs, TEAEs by severity, and TEAEs leading to study drug discontinuation. Summaries will be presented by MedDRA system organ class and preferred term using frequency counts and percentages. All safety analyses will be performed in the Safety Analysis Set.

### 7.4.7 Efficacy analyses (Cohort A and B)

#### 7.4.7.1 Primary and key secondary efficacy endpoint analyses

The categorical endpoints will be analyzed using the Chi-square test. Subgroup analyses, such as by gender, may be performed.

Continuous endpoints will be analyzed using the analysis of covariance models adjusted for the baseline value. Mixed model repeated measures models will be applied as sensitivity analyses.

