## 1.6 Study Rationale

PASC is a chronic, multi-organ disease predominantly characterized by fatigue and muscle weakness (Lopez-Leon 2021) potentially leading to significant impacts on individuals’ QoL, as well as their ability to be productive members of society insofar as it affects ability to work. The fatigue symptoms that patients with PASC experience is similar to chronic fatigue syndrome (Komaroff and Lipkin 2021).

AAs are known to catalyze a broad range of functions, including cellular metabolism, anti-oxidative signaling, differentiation, and cellular homeostasis, among others, across different organ systems and are therefore positioned to impact multiple pathophysiologies in this complex, systemic disease. Supplementation of AAs as single agents or high-order combinations has been reported to improve fatigue and muscle weakness (Wolfe 2017) and is hypothesized to improve PASC-fatigue via modulation of mitochondrial metabolism, redox imbalance, inflammation, and vascular insufficiency. AXA1125 (33.9 g BID), an orally active mixture of AAs, has the potential to alleviate fatigue in subjects with PASC compared to placebo. Results from previous studies have shown changes in bioenergetic state of tissue with administration of AXA1125 (Jason et al 2011).

To assess fatigue, this study utilizes the 6-minute walk test (6MWT) and Chalder Fatigue scale, which have been successfully validated and used in previous studies on chronic fatigue syndrome (Mantha et al 2020).

This is a pilot study, and the primary objective is to assess the efficacy and mechanism of action of AXA1125.

An interim look at the data from Cohort A indicated no association between Baseline fatigue score and Baseline PCr. Additionally, statistically significant improvement in fatigue scores using CFQ-11 prior to 6MWT did not correlate with changes in PCr recovery rate utilizing bimodal scoring at Week 4. Accordingly, CFQ-11 was determined to be appropriate primary end-point for the assessment of fatigue in Cohort B.

Moreover, in order to assess the relationship between AXA1125 and functional status, and to obtain valuable information on understanding the relationship between PCr and CFQ-11 results and

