### 2.3.2 Efficacy endpoints - Cohort B

- Change from baseline in subjects’ fatigue score as assessed by Chalder Fatigue Questionnaire (CFQ)-11 (by Bimodal Scoring) before a 6MWT at Week 4, and at Day 14 (without 6MWT)
- The proportion of subjects with an improvement in fatigue score as assessed by CFQ-11 before a 6MWT at Week 4
- Change from baseline in distance traveled during a 6MWT at Week 4
- The proportion of subjects with an improvement in distance traveled as assessed by 6MWT at Week 4

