###### Cohort B

An additional cohort (approximately 10 subjects) will be added to the study which will include subjects who were considered screen-failures for Cohort A due to their PCr recovery rate constant (< 50 seconds) provided their CFQ-11 Total Score is _≥_8 and meet the rest of the eligibility criteria.

The total study duration for each subject in Cohort B will be approximately 6 weeks, which will comprise a Screening Visit (1 week), Baseline Visit, a Treatment Period of 4 weeks, and a Follow-up Period of 1 week.

After obtaining informed consent, subjects will be re-screened and approximately 10 eligible subjects will be randomized in a 1:1 ratio (double-blind, placebo-controlled) to receive either twice daily (BID) oral administration of 33.9 g AXA1125 or a placebo.

Doses will be self-administered on Days 1 to 28, inclusive. Subjects will have clinic visits on Days 1, and 28, as well as telephone visits on Day 14, and 1 week after completion of study product administration.

The efficacy endpoints for Cohort B include the change from baseline at Week 4 in subjects’ fatigue score, as assessed by Chalder Fatigue Questionnaire (CFQ)-11 (by Bimodal Scoring) before 6 MWT, which will be evaluated at Screening, Baseline, and End of Treatment or Early Termination. CFQ-11 will also be assessed at Day 14 (without 6MWT). Additional endpoints for assessment of functional status, safety, and tolerability will be assessed. Details of randomization will be provided in the Randomization Plan and Interactive Response Technology (IRT) system.

Figure 2 Study Schematic - Cohort B

[figure not shown]

BID=twice daily; D=Day; PRO=patient-reported outcomes.

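### Cohort B's two responder proportions, at about 5 per arm, are assigned a chi-square test whose approximation no possible table supports; use an exact test or report them descriptively

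*Protocol*

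**What the plan says.** Protocol Section 7.4.7 is headed as applying to Cohorts A and B. Under it, Section 7.4.7.1 states: "The categorical endpoints will be analyzed using the Chi-square test". The synopsis says the same under its efficacy analyses for both cohorts. Neither place names a small-sample alternative or says whether a continuity correction is used. On the error level, Section 7.4.1 says: "There will be no multiplicity adjustment and all analyses will be performed at the 2-sided 0.05 level of significance".

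Section 7.1 sets the size of Cohort B: "Approximately 10 subjects (5 subjects per arm), who were considered screen-failures for Cohort A". Two of the four Cohort B endpoints in Section 2.3.2 are proportions. One is the proportion improved on CFQ-11 before the walk at Week 4. The other is "The proportion of subjects with an improvement in distance traveled as assessed by 6MWT at Week 4".

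On the rank of the endpoints, Section 1.6 says "CFQ-11 was determined to be appropriate primary end-point for the assessment of fatigue in Cohort B", and Section 1.5.2.3.2 says the same in nearly the same words. Section 2.3.2 and the synopsis list the Cohort B endpoints without calling any of them primary.

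**The concern.** The chi-square p-value is a large-sample approximation, usually relied on only when expected counts are at least about 5. With 5 subjects per arm that condition cannot be met, whatever the results. A nominally significant difference in a Cohort B proportion could then come from the approximation and not from the data. In a cohort this small, one subject decides whether a table crosses 0.05.

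The labelling point is separate. A reader of the rationale sections would expect one declared primary endpoint for Cohort B, and a reader of the endpoint list finds none.

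**Working it through.** **Inputs.** Chi-square test for both cohorts (7.4.7.1, synopsis); about 5 per arm (7.1), randomized 1:1 (3.1); two-sided 0.05 (7.4.1); two Cohort B proportions (2.3.2); missing binary data handled both as failures and by exclusion (7.4.3). The protocol gives no response rates for Cohort B, so any rate used below is an assumption.

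**Step 1: the plan's own figure.** The only sample size it derives is for Cohort A. With SD 10 and difference 10, n per arm = 2 × (1.960 + 0.842)² × 10²/10² = 15.7, rounded up to 16. That gives 32 evaluable and 32/0.8 = 40 enrolled, which matches Section 7.1. Cohort B has no corresponding calculation.

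**Step 2: expected counts.** With m responders among 10 subjects at 5 v 5, the expected counts in each arm are m/2 and (10 − m)/2. The smaller is largest at m = 5, where it is 2.5. At 4 per arm the ceiling is 2.0. In Cohort A at 20 per arm it can reach 10.

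**Step 3: the disputed tables.** For 3/5 v 0/5, chi-square = N(ad − bc)²/(n₁n₂m(N − m)) = 10 × (3×5 − 2×0)²/(5×5×3×7) = 2250/525 = 4.29, p = 0.038. The table 5/5 v 2/5 gives the same value. The other tests give:

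- Fisher: 2 × C(5,3)/C(10,3) = 20/120 = 0.167.
- Boschloo: 0.062. The tables at least as extreme are 3v0, 4v0, 5v0, 5v1, 5v2 and their mirrors, and their joint probability is maximised over the common response rate.
- Barnard (pooled statistic): the same ten tables, hence also 0.062. Software can return 0.058 for 3v0 if rounding drops the tied 5v2 tables.
- Yates-corrected chi-square: 10 × (15 − 5)²/525 = 1.90, p = 0.168.

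**Step 4: exact size of the uncorrected test.** The test rejects exactly those ten tables. At a common rate of 50% their probability is 2 × (10 + 5 + 1 + 5 + 10)/1024 = 62/1024 = 6.1%. Over other common rates p (the size at 1 − p is the same):

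| Common rate | Exact size |
| --- | --- |
| 10% | 1.0% |
| 20% | 3.8% |
| 25% | 5.0% |
| 30% | 5.8% |
| about 38% (maximum) | 6.2% |
| 50% | 6.1% |

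At 4 per arm the test rejects 4v0, 3v0, 4v1 and mirrors, and its maximum size is 2 × (1 + 4 + 4)/256 = 18/256 = 7.0%. At 4 v 5 it rejects the same tables as Fisher, with maximum size 3.9%. In Cohort A the maximum is 5.3% at 20 per arm and 5.8% at 16 per arm.

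**Step 5: what an exact test would do at 5 per arm.** Fisher and Boschloo both reject only 4v0, 5v0, 5v1 and mirrors. Their maximum size is 2 × (5 + 1 + 5)/1024 = 22/1024 = 2.1%. Power at assumed rates of 20% v 80% is 51% for uncorrected chi-square and 38% for the exact tests. At 30% v 70% it is 25% and 15%.

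**Step 6: the primary endpoint.** Sections 1.5.2.3.2 and 1.6 use the word primary for CFQ-11 in Cohort B. Section 2.3.2 and the synopsis list do not. Section 3.1 is closer to the rationale: it describes the Week 4 change in pre-walk CFQ-11 and refers to the remaining measures as additional endpoints.

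**The case against.** The strongest reply is that little is at stake. Cohort B is an unpowered add-on of about 10 subjects in a pilot study, and the maximum inflation at 5 per arm is 1.2 percentage points. Fisher's 0.167 also overstates the contrast, because that test is itself conservative here; the less conservative exact tests give about 0.062. Section 7.4.1 leaves details of the methods to the SAP, which could add a sparse-table rule. And 7.4.7.1 does not exclude a continuity correction, under which only 5v0 would be significant (maximum size 0.2%).

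Most of this stands as a limit on size. It does not remove the point, because the protocol names the test and its scope. Under the ordinary uncorrected reading, two splits are called significant that none of the exact tests supports. The Yates version would err heavily the other way.

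Three stronger readings are tempting but not supported:

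- **A reader might infer that the chi-square p-value is always too small at this sample size.** As an overall error rate, that fails: the size is below 5% for common rates under about 25% or over about 75%. Conditional on the total number of responders it is 2/252 = 0.8% with 5 responders and 20/120 = 16.7% with 3 or 7.
- **A reader might infer that the endpoint called primary is affected.** The CFQ-11 change score is continuous and is analysed by ANCOVA.
- **A reader might infer that any of four equal endpoints could become the Cohort B result, with the error rate of four independent tests.** Section 3.1 already singles out the Week 4 pre-walk CFQ-11 change. The two proportions are derived from the same CFQ-11 and walk measurements as the two change scores, so independence does not apply.

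**Conclusion.** The concern holds in a limited form. The protocol fixes a test for the two Cohort B proportions that no 5 v 5 table can justify by the usual expected-count rule. Assuming no continuity correction, the consequence is an exact size of up to 6.2% (7.0% at 4 per arm) for mid-range response rates, and p=0.038 for 3/5 v 0/5 and 5/5 v 2/5, where exact p-values run from 0.062 to 0.167. The expected-count result needs no assumption beyond 5 per arm; the power figures rest on assumed rates.

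The chi-square choice is not a general problem in Cohort A, where it would matter only with very high or very low proportions. The primary-endpoint mismatch is real, but it is mainly one of labelling and is minor.

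**What to change.** In Section 7.4.7.1 and the synopsis, specify an exact test (Boschloo or Fisher) for the Cohort B proportions and for any table with an expected count below 5. Alternatively, state that the Cohort B proportions are descriptive, with exact confidence intervals and no test. The descriptive option suits a cohort without a power calculation.

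The change is one of wording, but exact testing is not free. At 5 per arm the maximum size falls to 2.1%, and power at assumed rates of 20% v 80% falls from 51% to 38%.

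Separately, either label the Week 4 change in pre-walk CFQ-11 as the Cohort B primary endpoint in Section 2.3.2 and the synopsis, or delete the word primary from Sections 1.5.2.3.2 and 1.6. Either choice changes only text.

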### 7.4.8 Interim analyses and data monitoring (Cohort A only)

An interim analysis with potential sample size re-estimation will be performed when at least 10 subjects complete their Week 4 visit. Periodical administrative analyses may be performed to closely monitor the study.

### 7.4.9 Pharmacokinetic analyses (Cohort A only)

For all subjects in the study (Cohort A only), concentration data listings and descriptive statistics (arithmetic and geometric means, SD, coefficient of variation, median, minimum, and maximum) for fasted AAs (postdose plasma concentrations of AXA1125 dosed and non-dosed AAs) will be provided at all planned predose sampling time points. Concentrations determined for samples from ET visits, if any, and from the final clinic visit will be included in listings but not in descriptive statistics. For sampling time points, see the SOA (APPENDIX 1; APPENDIX 2).

In addition, the plasma concentration data from this study may be combined with data from other studies to perform a population PK analysis and exposure-response analyses, which will follow the principles outlined in the United States Food and Drug Administration (FDA) Guidance for Industry 2019 (FDA Guidance 2019) and may be reported separately.

Results from metabolite profiling analysis of leftover predose and postdose plasma PK samples will be reported separately, if applicable.

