#### 2.3.1.3 Exploratory efficacy endpoints

The exploratory efficacy endpoints are:

- Change from baseline in circulating mitochondrial peptides (eg, Mots-C), metabolomics, proteomics; plasma biomarkers of inflammation, adhesion markers, muscle injury (eg, troponins, creatine kinase, fibroblast growth factor-21) biomarkers, and mitochondrial function/metabolism (~1.5 mL total); nitric oxide biology; immune profiling, and metabolism/phenotypic extracellular acidification rate and oxygen consumption rate at Week 4
- The mean change from baseline in energetically active metabolites measured using proton magnetic resonance spectroscopy (1H-MRS; ie, creatine, intramyocellular lipids, acetyl-carnitine, and carnosine) at Week 4
- Change from baseline in predose plasma concentrations of AAs at Week 4 (see Laboratory Manual for details)
- The mean change from baseline in minimal intramuscular pH after exercise, initial PCr recovery rate, adenosine diphosphate (ADP) concentration at the end of exercise, maximal mitochondrial capacity, and other parameters measured using dynamic 31P-MRS at Week 4

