# 3 STUDY DESIGN

## 3.1 Overall Study Design

###### Cohort A

This is a minimum of one center, randomized, double-blind, placebo-controlled, pilot clinical study in the United Kingdom (Figure 1). The study will evaluate the efficacy and safety of AXA1125 in subjects with fatigue-predominant PASC (>12 weeks after initial infection).

The total study duration for each subject will be approximately 9 weeks. This study will comprise a Screening Period of up to 4 weeks, a Treatment Period of up to 4 weeks, and a Follow-up Period of 1 week.

After obtaining informed consent, subjects will be screened, and approximately 40 eligible subjects

(approximately 20 subjects per arm) will be randomized in a 1:1 ratio to receive BID oral administration of 33.9 g AXA1125 or a placebo. Doses will be self-administered on Days 1 to 28, inclusive. Subjects will have clinic visits on Day 1 and Day 28, as well as telephone visits on Day 14 and 1 week after completion of study product administration. Note: Doses should be self-administered at the clinic visit on Day 1 and Day 28 or End of Treatment (EOT)/Early Termination (ET).

The primary efficacy endpoint is the mean change from baseline at Week 4 in the PCr recovery rate following moderate exercise, as assessed by 31P-MRS, which will be evaluated at Screening and EOT/ET (Visit 4). Additional endpoints for assessment of muscle function, safety, tolerability, and exploratory efficacy endpoints will be assessed during the study

Details of randomization will be provided in the Randomization Plan and Interactive Response Technology (IRT) system.

Figure 1 Study Schematic - Cohort A

[figure not shown]

BID=twice daily; D=Day; MRS=magnetic resonance spectroscopy; PRO=patient-reported outcomes.

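### Section 7.4.9 promises amino acid summaries at every planned predose time, then confines the only on-treatment time to listings

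*Protocol*

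**What the plan says.** Section 7.4.9 (pharmacokinetic analyses, Cohort A only) makes two statements in succession. The first is that descriptive statistics for fasted amino acids "will be provided at all planned predose sampling time points". The second is that concentrations from any ET visit "and from the final clinic visit will be included in listings but not in descriptive statistics".

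The sampling plan is in Section 6.10: "For ALL subjects in the study, predose blood samples will be collected at Day 1 and at EOT/ET (Visit 4". On timing it adds: "Blood samples for AA concentration are to be collected no more than 30 minutes before administration of study drug", after a fast of at least 10 hours. A note in Appendix 3 says that amino acids are not collected at Screening.

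For the visit structure, Section 3.1 states for Cohort A: "Subjects will have clinic visits on Day 1 and Day 28". The Day 14 contact and the contact one week after the end of dosing are by telephone, and Appendix 1 labels Visits 3 and 5 accordingly.

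Section 2.3.1.3 lists among the exploratory efficacy endpoints: "Change from baseline in predose plasma concentrations of AAs at Week 4".

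Section 7.4.9 also describes the fasted concentrations to be summarised as "postdose plasma concentrations of AXA1125 dosed and non-dosed AAs". Its third paragraph refers to metabolite profiling of leftover PK plasma taken before and after dosing.

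**The concern.** A rule that keeps the final clinic visit out of PK summaries is harmless when that visit comes after treatment or when other on-treatment samples exist. Neither is true here. The final clinic visit is the Week 4 visit, and it provides the only amino acid sample taken during treatment. Followed literally, the rule summarises amino acids before treatment and nowhere else, although the sentence before it promises otherwise and a named endpoint needs the Week 4 value.

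At stake is whether the PK tables can describe how fasted amino acid concentrations stood after four weeks of AXA1125 or placebo. Whoever programs those tables must break one of the two sentences, and the protocol does not say which one governs.

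The postdose wording adds to the confusion. It describes samples that the schedule does not contain.

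**Working it through.** No formula or figure in the plan is involved. The check is a count of time points against the visit schedule.

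1. **Planned amino acid samples for PK** (Section 6.10; Appendix 3 note excluding Screening): Day 1 predose and Visit 4 predose. Count: 2.
2. **Which visit is the final clinic visit** (Section 3.1; Appendix 1 visit headings): Visit 2 on Day 1 is in clinic, Visit 3 on Day 14 is by telephone, Visit 4 on Day 28 is in clinic, and Visit 5 on Day 35 is by telephone. The last visit in the clinic is Visit 4, which is Week 4.
3. **What each sample represents** (Section 6.10): both are drawn within the 30 minutes before dosing. The Day 1 sample precedes any study drug and is the baseline. Visit 4 is the only on-treatment sample. So 2 = 1 baseline + 1 on-treatment.
4. **Apply the second sentence of Section 7.4.9.** Visit 4 is excluded whether it is reached as the Day 28 visit (final clinic visit) or early (ET visit). Time points left: 2 − 1 = 1, the baseline. On-treatment time points left: 1 − 1 = 0.
5. **Apply the first sentence instead.** Both planned predose time points are summarised: 2 of 2.
6. **Compare with the endpoint** (Section 2.3.1.3). A Week 4 change from baseline needs both values for the same subject. Under step 4 the PK summaries hold only one of them. Under step 5 they hold both.

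Could the final clinic visit mean something else? It cannot mean ET, because the sentence names ET visits separately. It cannot mean a later washout visit, because no clinic visit follows Day 28. The misaligned Visit 4 marks in the Appendix 1 table do not affect this, since Section 6.10 gives the sampling visits in words.

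For scale, Section 7.1 enrols about 40 subjects in Cohort A and assumes 20% dropout. That gives 40 × (1 − 0.20) = 32 subjects expected to reach Day 28, if dropout runs as assumed. Their Week 4 samples would be listed but not summarised in the PK tables.

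**Postdose wording.** The first paragraph of Section 7.4.9 calls the concentrations postdose and, in the same sentence, places them at predose time points. Section 6.10 schedules only predose amino acid samples. The third paragraph's leftover postdose PK samples therefore have no source in the schedule. Appendix 1 does plan metabolomic samples before and after exercise, but those are separate from the amino acid PK samples.

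**The case against.** The strongest reply is that little is lost. The amino acid change is listed as an efficacy endpoint, whereas the exclusion sits in the PK section and restricts only the descriptive statistics produced there. Section 7.4.1 provides descriptive statistics for continuous variables in general and leaves the comparison method for each endpoint to the SAP. Section 7.4.7 analyses continuous endpoints by ANCOVA adjusted for baseline. Its subheading names only primary and key secondary endpoints, so whether it covers this endpoint is arguable, but it does not exclude it. Section 7.4.9 itself allows the concentrations to enter a population PK or exposure-response analysis. The samples are still drawn, assayed and listed.

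This stands. A reader might infer that the Week 4 amino acid endpoint cannot be analysed or summarised at all. The documents do not support that: the restriction reaches only the Section 7.4.9 summaries, and within that section it is contradicted by the sentence before it.

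A reader might also infer that evidence on adherence would be lost. That is not supported either. Section 1.5.2.2 reports that 12 to 16 weeks of dosing did not meaningfully change mean fasted concentrations of the dosed amino acids in subjects with NAFLD, so a fasted predose sample is a weak marker of intake even when fully summarised. Adherence is followed by compliance review (Appendix 1) and drug accountability (Section 5.1.7).

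The reply does not remove the conflict. This is not detail left for the SAP. The protocol states a specific rule that does not fit its own schedule, and an SAP must depart from one of two adjacent sentences.

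**Conclusion.** The point holds as a contradiction within Section 7.4.9 and between that section and the Week 4 endpoint. If the exclusion governs, the PK descriptive statistics keep 1 of 2 planned time points and no on-treatment one, so they cannot describe the exploratory change from baseline. The conclusion rests on two readings, both stated in the text: amino acids for PK are sampled only on Day 1 and at Visit 4, and Visit 4 is the last visit in the clinic.

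The reach is small. One exploratory endpoint is affected, and only in its PK summaries. The primary and secondary endpoints are untouched. So is the exploratory objective of describing the baseline amino acid profile, because Day 1 is summarised under either sentence. The correction is worth making because the error is certain and the remedy costs almost nothing.

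**What to change.** In Section 7.4.9:

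- Remove the clause about the final clinic visit from the exclusion sentence. Day 28 (Visit 4) predose samples then enter the descriptive statistics and a change-from-baseline summary by arm, so 2 of 2 planned time points are summarised. Samples from true ET visits stay in listings only.
- In the first paragraph, change postdose to predose.
- In the third paragraph, remove the reference to leftover postdose samples.

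The cost is three small text edits. No additional samples, visits or assays are needed.
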